**Phase 2: ALTERED Trial**

The ALTERED trial is a randomised, double blinded, placebo controlled multi-centre study conducted in NHS Tayside & NHS Greater Glasgow & Clyde to compare allopurinol (dose to be confirmed from dose escalation study noted above) at either, 100mg, 200mg, 250mg, 300mg or 350mg to placebo.

Patients will be enrolled in this trial for a period of between 12 to 13 months.

At screening visit an initial history and clinical examination will be performed. Participants will then undergo an echocardiogram unless they have had an echo in the previous 2 years. Eligible participants will have to have echo defined LVH as per American Society of Echocardiography criteria of LVM ≥115g/m^2^ for men and >95g/m^2^ for women.

Should the participant have echo defined LVH, they will return for a Cardiac Magnetic Resonance Imaging (MRI) scan at a later date in the screening period, prior to their baseline (Randomisation) visit.

They will also have bloods taken for safety analysis, have a 12 lead ECG done and have 24 hour BP monitoring and vital signs recorded.

Once the patient is known to be eligible they will return - for the first randomisation, dosing visit at any time up to four weeks after screening. At this randomisation visit post dialysis session, eligible participants will be randomly assigned to either placebo or allopurinol 100mg.

They will continue on allopurinol/placebo 100mg for 2 weeks, with dosing after each dialysis session only. They can have FMD, PWV and PWA measurements taken. All participants will be offered the opportunity to opt in or out of the FMD, PWV and PWA measurements which are secondary outcome measures only.

If study drugs are tolerated, the dose would be increased at weekly intervals after the 200mg dose to the allopurinol dose chosen by the dose escalation study, if greater than 200mg. Baseline blood samples will be taken for full blood count, renal function, liver function, random blood glucose, haemoglobin A1C, lipids, calcium and phosphate, and these will be repeated at 6, 9 and 12 months, bar lipids which are tested at baseline and final visit only. However, urate levels will be stored and measured at the end of the study in order to ensure blinding throughout. Subjects will be followed at baseline, week 2, week 6, month 6, month 9 and 12 with close monitoring of their full blood count and renal function. Research bloods for BNP measurement and inflammatory markers will be taken at baseline, and at months 6, 9 and the final 12 month study visit. Office BP will be measured thrice at each visit and the average of the second and third reading will be recorded. Furthermore pre and post dialysis. BP is recorded as part of standard care and will be available for analysis. 24 hour BP will also be measured at baseline and at 12 months.

Patients will continue with all their usual medication, which will remain unchanged throughout unless clinically indicated.

**CMRI Methods**

The MRIs will always be done on a post-dialysis day. Baseline and repeat CMR examinations in screening (between 1-4 weeks before randomisation) and after the final 12 month (+/- 2 weeks) visit will be performed on similar 3T Magnetom scanners (Siemens, Erlangen, Germany) using dedicated phase array cardiac and phosphorous spectroscopy coils. Serial contiguous short-axis cines will be acquired from the vertical long axis and horizontal long axis of the left ventricle (electrocardiogram gated, steady-state free precession imaging [true fast imaging with steady-state precession], with the short axis imaging parameters being a repetition time of 2.5ms, echo time of 1.1ms, flip angle of 60°, and slice thickness 6mm). Analysis will be performed offline (Argus Software, Siemens) by a single blinded observer for the assessment of ventricular volumes (EDV, ESV, stroke volume), EF, and left ventricular mass. This single observer will analyse scans from both sites. The reproducibility of the left ventricular mass assessment using MRI will be derived for this observer. A test-retest intraobserver coefficient of variation of 2.0% is usual in our past MRI studies. We will also assess reproducibility between each site, although the same observer will assess all scans at both sites. We will take the opportunity to measure two other MRI parameters of interest which are easily obtained with little extra scan time: Phosphorous -31 MR spectroscopy and aortic compliance by methods already published by us.[[29](#_ENREF_29), [30](#_ENREF_30)] Both will give significant added value.

MR spectroscopy will see whether allopurinol increases high energy phosphates in ESRD (measured by PCr:ATP) which it is likely to do since it is known to increase ATP levels in vitro and it is now known to improve cardiac energetics (MRI measured) in human heart failure.[[31](#_ENREF_31), [32](#_ENREF_32)] We will measure high energy phosphates (HEP), comparing Phosphocreatine : Beta adenosine triphosphate (PCr:ATP) ratio from the long axis views of the left ventricle.[[29](#_ENREF_29)] In addition we will use MRI to assess aortic vascular compliance and pulse wave velocity [[30](#_ENREF_30)] using cine transverse thoracic aortic gated steady state free precession acquisitions which will complement well the other peripheral vascular measures of endothelial/vascular function being assessed (see below).

**FMD**

FMD will be offered to all participants in the main trial, but may be declined without affecting their participation in the main trial.

FMD on the brachial artery will be performed in the non-fistula arm on three visits (baseline, month 9 and month 12) using a Philips iE33 ultrasound machine (Phillips Medical Systems, United Kingdom) according to the guide-lines set by the International Brachial Artery Reactivity Task Force.[[33](#_ENREF_33)] The brachial artery will be longitudinally imaged above the elbow using an 11.3-MHz probe. The image will be recorded for 2 minutes, followed by induction of forearm ischaemia by inflating a cuff below the elbow to 200 mmHg (or 50 mmHg above SBP, whichever is higher) for 5 minutes and deflating rapidly. The resulting reactive hyperaemia will be recorded for a further 2 minutes. After a rest period of 10 minutes, the procedure will be repeated, with 0.4mg of glyceryl trinitrate being administered sublingually to determine endothelium-independent dilation. FMD will be expressed as per cent change in diameter relative to the baseline diameter at rest. Analysis of all FMDs will be performed on the Brachial Analyser version 5.0 software (Medical Imaging Applications, LLC) by a single trained investigator (the clinical research fellow) to avoid inter-observer variability. This investigator will be blind to allocated treatments. Our intra-observer coefficient of variation for FMD is usually 5.2%. Two factors should ensure reliable results despite there being two sites : each patient will always be studied on the same equipment and the same individual (the research fellow) will do all the tests and interpret them (blindly) at both sites. For further reassurance, blinded ultrasound scans will be re-analysed to ensure good reproducibility at each site and between sites.

**Applanation Tonometry**

PWA will be offered to all participants in the main trial, but may be declined without affecting their participation in the main trial.

Pulse wave analysis (PWA) and PWV will be determined in the non-fistula arm by recording the radial waveforms and radial-carotid waveforms, respectively, at three visits (baseline, month 9 and month 12) using the Sphygmocor system. The central AIx will be corrected to a heart rate of 75 beats/min. A single trained investigator (the clinical research fellow) who is blind to the allocated treatment will perform the PWA and PWV at both sites. We will also use bio-impedance at the same time to measure total body water in MRIs done at Glasgow sites.[[21](#_ENREF_21)] . This will complement the end diastolic volume data from the MRI at both sites. In our index study, EDV fell but we did not know if this was due to afterload reduction or to a global fall in body water.[[21](#_ENREF_21)] Bio-impedance will help determine this.

**Research Blood tests**

Research bloods will be taken at baseline and at the end of treatment phase for BNP and inflammatory markers.

**Adverse events**

Adverse events will be sought by symptom enquiry at each visit and by monitoring of routine blood samples.

# STUDY POPULATION

## NUMBER OF PARTICIPANTS

For the Phase 1 Dose escalation study 10 eligible patients will be recruited from the dialysis sessions at any of the three NHS Tayside locations (Ninewells Hospital, Arbroath Royal Infirmary and Perth Royal Infirmary) or at six locations in Greater Glasgow & Clyde (Western Infirmary, Victoria Infirmary, Stobhill Hospital, Royal Alexandra Hospital, Inverclyde Royal, & Vale of Leven) by the clinical research fellow, who is a nephrology registrar.

For the Phase 2 ALTERED Trial 76 eligible patients will be recruited from the dialysis clinics at the two health boards.

It is anticipated that it will take three months to recruit and complete the Phase 1 dose escalation study and one year to recruit 76 eligible patients with approx. 114 being consented in the Phase 2 trial. We anticipate a screen failure rate of 25% and a dropout rate of 10% after recruitment.

## INCLUSION CRITERIA

They will be eligible if they

- are aged 18 to 80 years
- end stage renal disease (CKD stage 5 eGFR <15ml/min /1.73m^2^)
- been on haemodialysis for at least 3 months.
- For main study also require echocardiographic LVH according to the ASE (American Society of Echocardiography) criteria of LVM ≥115g/m^2^ for men and >95g/m^2^ for women.

## EXCLUSION CRITERIA

Exclusion criteria are

- Known heart failure
- Left Ventricular Ejection Fraction <45%,
- already had gout or on allopurinol,
- severe hepatic disease
- or on azathioprine, 6 mercaptopurine, theophylline or warfarin.
- malignancy or other life threatening diseases,
- pregnant or lactating women
- any contraindication to MRI (claustrophobia, metal implants).
- with a planned (relative) kidney transplant,
- Aged than 18 or over 80 years
- Above ankle amputees
- Patients who have participated in any other clinical trial within the previous 30 days will be excluded.
- Patients who are unable to give informed consent will also be excluded from this trial.
- Any other considered by a study physician to be inappropriate for inclusion

# PARTICIPANT SELECTION AND ENROLMENT

**(See CONSORT Diagram Appendix 4)**

## IDENTIFYING PARTICIPANTS

Participants will be recruited from current attendees at the dialysis clinics at Ninewells Hospital, Arbroath Royal Infirmary and Perth Royal Infirmary, and at six sites in Greater Glasgow & Clyde (Western General Infirmary, Victoria Infirmary, Stobhill Hospital, Royal Alexandra Hospital, Inverclyde Royal & Vale of Leven)

The research fellow or trial manager/research nurse will screen both the clinic lists and medical notes to identify suitable people (see below).

## CONSENTING PARTICIPANTS

Approaching potential participants and then obtaining consent will be carried out by the research fellow or trial manager/research nurse. The fellow or trial manager will approach suitable participants either at dialysis sessions or by letter sent from their renal consultant. Participants will be provided with a full participant information sheet (PIS). All participants will be given at least 24 hours to consider their response, which will initially be given either orally at the clinic or in writing by returning an expression of interest in a stamped addressed envelope. A screening visit will then be arranged where participants will be able to ask any questions about the study. If they decide to participate, informed consent will be taken and eligibility by all the criteria confirmed.

## SCREENING FOR ELIGIBILITY

Participants must have documented ESRD and be attending haemodialysis sessions Participants will be consented prior to screening and a screening log will be maintained.

## INELIGIBLE AND NON-RECRUITED PARTICIPANTS

The reason(s) for ineligibility will be explained to participants and any questions they have will be answered. They will be thanked for their participation in screening and any relevant information from this will be added to their hospital notes and be communicated to their GP and nephrologist where the patient consents for this to happen.

## RANDOMISATION

### Randomisation

There is no randomisation in the phase 1 dose escalation study. It is an open label study.

**For the main Phase 2 ALTERED trial:**

Participants will be allowed to continue all their usual medication throughout.

After successful screening for eligibility and safety, participants will be randomised to either allopurinol or placebo in a double blind fashion. Participants and their bloods (U&Es, LFTs, FBC) will be monitored as per study schedule and medication stopped or reduced in dose if concerns arise. If study drug dose is reduced, they will remain in the study. If study drug needs to be stopped, they will remain in the study in order to do an “intention to treat” analysis.

Double blind medication (allopurinol or placebo) will be prepared, packaged and labelled by Tayside Pharmaceuticals. The medication will come labelled as “Participant 1”, “Participant 2”, etc. and will be distributed to the participant by the research fellow according to their sequence number. Randomisation will be carried out by Tayside Pharmaceuticals using block randomisation. They will use a validated randomisation program and will securely backup both the randomisation seed and the randomisation allocation. Two copies of the allocation will be supplied with the IMP & placebo tablets to the Clinical Trials Pharmacy, Ninewells, and to the Clinical Trial Pharmacy at Western Infirmary, Glasgow who operate a 24 hour emergency unblinding facility.

### Treatment Allocation

Participants will be given blinded medication. At the randomisation visit they will be dosed with either allopurinol 100mg or matched placebo.

They will then be asked to take one tablet after each dialysis session for two weeks (+/-2 days).

Thereafter the medication will be increased weekly (after 3 dialysis sessions) as tolerated (+/- 2 days) to the dose decided in the pilot study – ie one week at 200mg, one week at 250mg, one week at 300mg and upto 350mg, or placebo as determined by pilot data.

Compliance will be checked and documented using tablet counts at each visit. If non-compliant, they will be encouraged to become compliant. If they persist as non compliant, (<70% compliant) they will stay in the study, but not on study medication, in order to do an “intention to treat” analysis.

### Emergency Unblinding Procedures

A clinician familiar with the research (and named on the delegation log) will be available each workday for contact by all participants. This will include the CI, the PI and a nominated other research fellow based within the Division of Cardiovascular & Diabetes Medicine department at Ninewells and at BHF Cardiovascular Research Centre, University of Glasgow. Any other clinician who sees participants in the study will be free to stop the study drug if they feel it is clinically indicated and may contact the Clinical Trials Pharmacy Department, Ninewells or at the Western Infirmary in Glasgow to break the code if they feel it is necessary. However side effects tend to be minor (see section 6 below) and therefore emergency unblinding is highly unlikely. The Ninewells and Western Infirmary Pharmacy departments run an out of hours service for doctors to contact, if necessary in emergency. We will follow TASC SOP40 giving details of how to unblind, who can do it and where contacts for unblinding can be found.

### Withdrawal procedures

Side effects are likely to be minor and expected and it will therefore be a participant choice as to whether they withdraw or not from a study. Rash is the main side effect and withdrawal will occur if it is marked as persistent. Participants who withdraw will be replaced if possible within the study timeframe. Contact (by telephone) will be maintained by the research fellow/trial manager/research nurse with those who withdraw to ensure resolution of adverse event(s). The reasons for withdrawal will be noted in the participant’s CRF and casenotes. If withdrawal is due to an AE it will be logged as such on the Adverse Event Log.

Participants are free to withdraw from the study at any time. The reasons, if known, will be recorded in the medical casenotes and CRF.

# INVESTIGATIONAL MEDICINAL PRODUCT

## STUDY DRUG

### Study Drug Identification

Allopurinol Ph Eur 100mg, 200mg, 250mg, 300mg and 350mg enclosed in a hard gelatine capsule pack.

Placebo capsules containing Lactose Ph Eur to match the actives in a hard gelatine capsule pack.

### Study Drug Manufacturer

Tayside Pharmaceuticals, Ninewells Hospital, Dundee.

### Marketing Authorisation Holder

Not applicable. IMP dossier to be formulated by Tayside Pharmaceuticals

### Labelling and Packaging

Tayside Pharmaceuticals, Ninewells Hospital, Dundee.

### Storage

Drugs will be stored in the Clinical Trial Pharmacy (Ninewells Hospital) and a small supply in the Division of Cardiovascular and Diabetes Medicine Local Drug Storage Area. This latter area is subject to audit by the Clinical Trials Pharmacy, Ninewells Hospital. Two sets of drug accountability logs will be held. Storage in Glasgow will by via the Clinical Trials Pharmacy at Western Infirmary Glasgow.

### Summary of Product Characteristics

The Summary of Product Characteristics (SmPC) will be filed appropriately in the Trial Master File (TMF), ISFs and Pharmacy Site File (PSF) and be updated regularly. Allopurinol will however be given outwith its usual clinical use (off-label).

### Accountability procedures

These will be overseen by the Clinical Trials Pharmacist in the Clinical Trials Pharmacy Department (Ninewells Hospital). This will be documented as such in the TMF and Accountability Logs will be held in the TMF. We will follow the standard TASC policy on drug accountability in CTIMPs.

## STUDY COMPARATOR

### Comparator Identification

Placebo capsules (with an identical appearance to the active drug) and containing only lactose.

### Comparator Manufacturer

Tayside Pharmaceuticals, Ninewells Hospital, Dundee.

### Labelling and Packaging

Tayside Pharmaceuticals, Ninewells Hospital, Dundee.

### Storage

Drugs will be stored in the Clinical Trial Pharmacy (Ninewells Hospital) and a small supply in the Division of Cardiovascular and Diabetes Medicine Local Drug Storage Area. This latter area is subject to audit by the Clinical Trials Pharmacy, Ninewells Hospital. Two sets of drug accountability logs will be held. Storage in Glasgow will by via the Clinical Trials Pharmacy at Western Infirmary Glasgow.

## DOSING REGIME

Participants will be given blinded medication. At the randomisation visit they will be dosed with either allopurinol 100mg or matched placebo.

They will then be asked to take one tablet after each dialysis session for two weeks (+/-2 days).

Thereafter the medication will be increased weekly as tolerated (+/- 2 days) to the dose decided in the phase 1 dose escalation study – ie one week at 200mg, one week at 250mg, one week at 300mg and upto 350mg, or placebo as determined by pilot data.

Compliance will be checked and documented using tablet counts at each visit. If non compliant, they will be encouraged to become compliant. If they persist as non compliant (<80% compliance), they will stay in the study, but not on study medication, in order to do an “intention to treat” analysis.

## DOSE CHANGES

If there is any significant deterioration in U&Es or LFTs, as considered by a trial physician, then the dose will be stopped and they will not receive any further IMP. If the participant is taken off the study their GP and consultant nephrologist will be informed of the abnormal blood results or further monitoring though the patient will remain in the study for the entire duration even if study medications are stopped.

**.**

## PARTICIPANT COMPLIANCE

Compliance will be checked and documented using tablet counts at each visit. Should compliance be poor the patient will be advised by the research fellow on the importance of correct compliance. Should compliance be less than 70%, they will be withdrawn from treatment.

## OVERDOSE

This is unlikely given the simple once daily dosing but there is no specific antidote. As noted in the SmPC, ingestion of up to 22.5 g allopurinol (i.e., the equivalent of 64 maximum dose 350mg study drug capsules) without adverse effect has been reported. Symptoms and signs including nausea, vomiting, diarrhoea and dizziness have been reported in a patient who ingested 20g allopurinol. Recovery followed general supportive measures. Massive absorption of allopurinol may lead to considerable inhibition of xanthine oxidase activity, which should have no untoward effects unless affecting concomitant medication, especially with 6-mercaptopurine and/or azathioprine. Adequate hydration to maintain optimum diuresis facilitates excretion of allopurinol and its metabolites. If considered necessary further haemodialysis may be used.

## OTHER MEDICATIONS

### Permitted Medications

Other medications (save for those listed in 6.7.2) will be allowed. All concurrent medication(s) will be recorded.

### Prohibited Medications

6-mercaptopurine or azathioprine: concurrent prescription of either of these drugs would not be allowed due to the known interaction of these drugs with allopurinol. Any participants already on these drugs would be excluded at screening. If they needed to start on treatment with either of these whilst receiving study medication then they would be withdrawn from study.

Warfarin: due to the possible influence of allopurinol on warfarin levels (requiring increased frequency of monitoring) any participants already on a stable dose of this drug would be excluded at screening. If they needed to start on treatment with warfarin whilst receiving study medication then this would however still be possible (as any patient newly commenced on warfarin has frequent monitoring of their INR).

Theophylline: due to the possible influence of allopurinol on theophylline levels any participants already on this drug would be excluded at screening. If they needed to start on treatment with theophylline whilst receiving study medication then they would be withdrawn from study.

Ampicillin/amoxicillin: not prohibited, but an increase in frequency of skin rash has been reported among s receiving ampicillin or amoxicillin concurrently with allopurinol compared to patients who are not receiving both drugs. The cause of the reported association has not been established. However, in participants receiving allopurinol an alternative to ampicillin or amoxicillin will be used where available.

The GP information letter and PIS will contain information on all the above points.

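### Section 6.7.2 takes patients out of the study when only study drug has to stop, so the month 12 MRI that section 5.5.1 means to keep is lost

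*Protocol*

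**What the plan says.** Section 6.7.2 (Prohibited Medications) covers drugs started during the trial. For theophylline: "If they needed to start on treatment with theophylline whilst receiving study medication then they would be withdrawn from study". For 6-mercaptopurine and azathioprine: "If they needed to start on treatment with either of these whilst receiving study medication then they would be withdrawn from study". Warfarin may be started without leaving.

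Elsewhere the protocol separates stopping study drug from leaving the study:

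- Section 5.5.1, for the main Phase 2 trial: "If study drug needs to be stopped, they will remain in the study". The stated purpose is an intention-to-treat analysis.
- Sections 5.5.2 and 6.3, for persistent non-compliance: "they will stay in the study, but not on study medication".
- Section 6.4, for worsening U&Es or LFTs: "though the patient will remain in the study for the entire duration even if study medications are stopped".
- Section 6.5, for poor compliance: "Should compliance be less than 70%, they will be withdrawn from treatment".

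Section 5.5.4 (Withdrawal procedures) says of side effects that "it will therefore be a participant choice as to whether they withdraw or not from a study". It continues: "Rash is the main side effect and withdrawal will occur if it is marked as persistent. Participants who withdraw will be replaced if possible". Telephone contact is then kept with those who withdraw so that adverse events are seen to resolve.

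**The concern.** A patient who must start azathioprine, 6-mercaptopurine or theophylline has to come off allopurinol. Section 5.5.1 keeps that patient in follow-up and section 6.7.2 removes the same patient. Two sites could therefore handle identical cases differently, each following the protocol.

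The primary outcome makes this matter. Under CMRI Methods in section 3, and in the Appendix 3 schedule, LV mass is measured only at screening and after the month 12 visit. There is no interim scan. A patient removed in between contributes no post-baseline LV mass at all. Section 9.3 keeps that patient in the intention-to-treat analysis by imputation, but an imputed value then stands where a measured one could have been obtained. The completed-cases analysis, also planned in section 9.3, loses the patient altogether.

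For the prohibited drugs the protocol gives no reason to expect more starts in one arm than in the other. Rash is different. Section 5.5.4 names it as the main side effect, so losses under that rule may be more frequent on allopurinol.

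**Working it through.** **1. The plan's own sample size (background).** Inputs from section 9.1: difference 10 g, SD 12 g, 90% power, p<0.05. Two-sided testing is assumed because the section does not say.

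- Normal approximation: n per group = 2 × (1.960 + 1.282)² × (12/10)² = 2 × 10.51 × 1.44 = 30.3, rounded up to 31.
- Two-sample t-test: 31.25, rounded up to 32, with power 0.907 at 32 v 32.

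The stated 32 per group is reproduced.

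**2. The rules side by side.**

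| Section | Trigger | Study drug | Follow-up |
|---|---|---|---|
| 5.5.1 | drug needs to be stopped (Phase 2) | stopped | continues |
| 5.5.2, 6.3 | persistent non-compliance | stopped | continues |
| 6.4 | worsening U&Es or LFTs | stopped | continues |
| 6.5 | compliance below 70% | stopped | not ended by this wording |
| 6.7.2 | azathioprine, 6-mercaptopurine, theophylline | stopped | ends |
| 5.5.4 | persistent rash | stopped | not stated; most naturally ends |

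Section 6.5 shows that the protocol has wording for a drug-only stop and does not use it in section 6.7.2. Section 5.5.1 might be read narrowly, as covering only stops prompted by blood monitoring. Section 6.7.2 would still depart from 5.5.2, 6.3 and 6.4 without a reason for ending follow-up.

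In section 5.5.4 the rash sentence does not say what the patient withdraws from. The sentence before it is about leaving a study, and those after it provide for replacement and telephone contact. Leaving the study is the natural reading, though not the only one.

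**3. Possible shift in the treatment difference.** The protocol gives no rate for these events and no imputation error, so both are assumed. Let k of the 38 patients in one arm be withdrawn, and let each imputed LV mass be wrong by e grams in the same direction. Then shift = k × e / 38. The range is k = 1 to 4 and e = 0 to 10 g, where 10 g equals the whole planned effect.

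| k | share of arm | e = 0 | e = 5 g | e = 10 g |
|---|---|---|---|---|
| 1 | 1/38 = 2.6% | 0 | 0.13 g | 0.26 g |
| 4 | 4/38 = 10.5% | 0 | 0.53 g | 1.05 g |

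Standard error of the difference with 38 per arm: 12 × √(2/38) = 2.75 g. The largest shift is 1.05 / 2.75 = 0.38 of a standard error.

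**4. Power.** The protocol carries two attrition figures, so both are shown.

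- Appendix 4 projects 4 lost per arm, leaving 34 v 34: t-test power 0.923. One further loss, 33 v 34, gives 0.919.
- Section 9.1 allows 10% death or transplantation plus 10% dropout: 76 × 0.80 = 60.8 evaluable, power 0.901 by the normal approximation. Two further losses, 58.8 evaluable, give 0.892, or about 0.5 percentage points per patient.

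On either basis power moves little.

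**The case against.** The strongest reply is that section 6.7.2 is loosely worded. Section 6.4 speaks of a participant being taken off the study in a sentence that then keeps the participant in it, so the protocol sometimes says study where it means study drug. Read as a whole, with 5.5.1 governing Phase 2, section 6.7.2 may be the same slip. Section 6 also serves the open-label Phase 1, which has no MRI and no intention-to-treat analysis, so leaving the study does no harm there. This may explain how the wording arose, but it does not remove the conflict. Section 6.4 corrects itself within its own sentence. Section 6.7.2 does not, and nothing limits it to Phase 1.

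The rash point is an inference, which is fair to say. Persistent rash could fall under the concerns that lead to stopping drug in 5.5.1, with follow-up continuing. That part is a request for clarification, although the possible imbalance between arms rests on it.

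The effect is also likely to be small. Section 4.3 excludes current users of these drugs and patients with a planned (relative) transplant, attrition is already allowed for, and section 9.3 keeps withdrawn patients in the main analysis. All of this stands and limits the weight of the point. Leaving the imputation method to the SAP is no fault. An SAP cannot, however, recover a scan that was never done.

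Finally, attendance at month 12 by someone newly needing these drugs is not assured. That is true, but a protocol rule that ends follow-up makes the loss certain.

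**Conclusion.** The concern holds. For azathioprine, 6-mercaptopurine and theophylline, section 6.7.2 contradicts section 5.5.1 and the approach taken in 5.5.2, 6.3 and 6.4. For persistent rash, section 5.5.4 is ambiguous and leans the same way as 6.7.2.

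The result is missing primary-outcome data that the protocol itself creates and that its intention-to-treat aim argues against. The size is small as far as it can be bounded: 0 to 1.05 g on the treatment difference, at most 0.38 of a standard error. The upper end needs four withdrawals in one arm, each imputed value wrong by the full planned effect in the same direction. The actual number of withdrawals and the actual bias cannot be derived from the protocol. The change should be made because it is cheap and keeps measured data, not because a large bias has been shown.

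**What to change.** - **Section 6.7.2, both places:** state that study drug is stopped and that, in Phase 2, the participant stays in follow-up to the month 12 MRI.
- **Section 5.5.4:** state that for persistent rash study drug is stopped and the participant stays in follow-up to the month 12 MRI. Limit withdrawal from the study to participants who withdraw consent to follow-up.
- **Section 6.4:** replace the reference to being taken off the study with being taken off study drug.

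The cost is protocol wording in three sections. The month 12 visit and MRI are already scheduled for every randomised participant in Appendix 3, so no assessment is added. Participants remain free to withdraw at any time.
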